#### Analysis population

The primary and secondary endpoints will be analyzed on the intention-to-treat (ITT) set, consisting of all patients randomized in the study independent of the intervention they receive (analysis “as randomized”). The safety analysis will be performed on the safety set, consisting of all patients randomized into the study and assigned to the treatment group of their actual treatment.

#### Analysis of the primary endpoint measure

Preoperative supportive parenteral nutrition will be tested for superiority over no supportive nutrition during NACT with respect to the absolute value of CCI on postoperative day 30 using Fisher’s exact test with the following hypothesis:$$ H0:a=0\  vs. HA:a\ne 0 $$

Where “a” denotes the difference of the distribution of CCI values in both patient groups. The distribution will be compared using the Wilcoxon signed-rank test. The test will be performed two-sided and with a global significance level of 5%.

#### Sensitivity of the primary endpoint measure

Missing primary endpoint data will be imputed conservatively. For sensitivity analysis, the primary endpoint analysis will be repeated in the per-protocol (PP) population. The PP population includes all patients of the ITT population “as treated.” Patients who did not complete visit 9 will be excluded.

#### Analysis of secondary endpoint measures

Secondary endpoints will be analyzed by treatment arm on the ITT set, using appropriate descriptive statistics. Any explorative statistical testing will be performed using a significance level of 5%.

#### Safety analysis

All AE/SAEs will be analyzed with incidence rates by treatment group and according to their severity. All AE/SAEs rated as related to the study treatment will be listed separately. For the comparisons between groups, the Chi-square test and Fisher’s exact test will be used if appropriate. All patients who started visit 2 will be analyzed “as treated.”

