### Interventions

#### Experimental intervention

In the experimental group, patients will receive supportive parenteral nutrition containing 600 kcal per day via a central line (e.g. intravascular port system) in addition to their regular enteral nutrition. The enteral nutrition will be documented in a specific “nutrition diary.” For the parenteral nutrition, multi-chamber-bags containing amino acids, glucose, and lipids have to be used. On demand, vitamins, electrolytes, and micronutrients (trace elements) can be added. The choice of product is left to the local home care service and is not bound to a specific manufacturer. If the patient is unable to achieve his daily calorie requirement by enteral nutrition, the missing calories will be added to the 600 kcal of parenteral nutrition. A dietary assistant or a member of the study team will recalculate the daily calorie requirement once weekly, in the framework of the routine clinical evaluation during the NACT. The daily calorie requirement is calculated as follows:women: 25 kcal/kg of the ideal body weight (IBW)men: 30 kcal/kg of the IBW

The daily supportive parenteral nutrition will start with the first day of preoperative chemotherapy until the day of surgery. The administration will be effectuated by qualified nurses and can take place at the patient’s home if an ambulatory home care service is organized. The beginning of the supportive nutritional therapy will be documented in the electronic case report form (eCRF). In addition, the home care service will record the administration on a separate log.

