In addition, the following outcome measures have been defined as secondary endpoint measures: (1) rate of serious adverse events (SAEs) and adverse events (AEs) during NACT according to the Common Terminology Criteria for Adverse Events (CTCAE v4.03.); (2) rate of AEs/SAEs associated with the administration of parenteral nutrition according to CTCAE v4.03; (3) morbidity and mortality within 30 days postoperatively according to the Calvien Dindo classification (Table 1) [19]; (4) quality of life (QoL) according to the results of EORTC (European Organization for Research and Treatment of Cancer) QLQ-C30 questionnaire; (5) change of weight and body mass index (BMI); (6) length of postoperative hospital stay; and (7) length of postoperative ICU say.

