### Data collection and management

The applicable local regulations of data privacy protection will be followed. Before inclusion, patients will be informed that any patient-related data and materials will be appropriately pseudonymized (pursuant to GCP regulations [16]) and that these data may be used for analysis and publication purposes. All trial data will be recorded in eCRFs. After inclusion, baseline data (demographical data, medical history, anthropometric data) will be documented accordingly. A physical exam will be performed and a routinely taken blood sample analyzed (see Fig. 2 for included parameters). The EORTC QLQ-C30 questionnaire for the assessment of QoL will be documented and “nutrition diaries” will be handed out and explained to all participants. In case of women with childbearing potential, a pregnancy test will also be performed. During NACT, three study visits will be performed where ECOG score, as well as AEs and SAEs will be assessed and documented in the eCRF. At visit 3 (pre-chemotherapy), data on the type, duration, and dosage of chemotherapy and any additional radiotherapy will be documented. In addition, parameters of the planned parenteral nutrition intervention, the planned application route (e.g. via intravenous port system) and the used product will be documented for patients in the experimental group.

Furthermore, the IBW will be calculated as follows:IBW men: 50 kg + (2.3 kg * [body height (in cm) – 152.4 cm]/2.54 cm); andIBW women: 45.5 kg + (2.3 kg * [body height (in cm) – 152.4 cm]/2,54 cm).

Subsequently the required daily calorie supply can be calculated as:IBW * 30 kcal for men; andIBW * 25 kcal for women.

At visit 4 after the first half of chemotherapy, ECOG score, AEs, and SAEs will be assessed for all patients. In addition, anthropometric data will be reassessed and nutrition diaries will be collected and the enteral calorie intake documented. In the control group, the nutritional risk will be reassessed using the NRS 2002 screening. If control group patients fail to meet 25–50% of their calorie demand by enteral nutrition alone, parenteral nutrition will be initiated according to the procedures in the experimental group.

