### Safety evaluation and reporting of adverse events

All AEs/SAEs from the moment of randomization until the last study visit have to be assessed, documented, and reported by the local clinical investigator or designated sub-investigator. Postoperative complications and surgical complications do not have to be documented as AE/SAE, but will be documented according to the Clavien Dindo Classification (visits 7–9). During preoperative chemotherapy (visits 2–5), changes of laboratory parameters that are expected because of the underlying illness and that are graded < 3 according to CTCAE v4.03 do not have to be reported as AEs.

SAEs have to be reported within 24 h and will be classified by intensity, outcome, and causality. Exceptions are: (1) hospital treatment planned before inclusion in the study; (2) planned admission to the hospital for NACT; and (3) hospital admissions because of the underlying disease as long as they are not because of an aggravation of the disease.

All SAEs will be subject to a second assessment by a designated person who will be independent from the reporting investigator and the trial sponsor. According to AMG and GCP regulations, the ethics committee and the competent federal health authority will be informed of all suspected unexpected serious adverse reactions (SUSARs) and all SAEs resulting in death or being life-threatening. Safety reports resuming all AE/SAEs have to be compiled regularly by the principal investigator to reassess the risk–benefit analysis.

If a female participant gets pregnant during the trial, the investigator has to report the pregnancy to the sponsor within 24 h after becoming aware of it. It is recommended to follow-up on the pregnancy and outcome.

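### Daily nurse contact comes only with parenteral nutrition, so the crude comparison of all adverse events is at risk of unequal capture of grade 1-2 events, most plausibly against parenteral nutrition

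*Protocol article*

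**What the plan says.** All references are to the protocol article.

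- **Contact in the experimental arm.** Under Experimental intervention: "The daily supportive parenteral nutrition will start with the first day of preoperative chemotherapy until the day of surgery". On who gives it: "The administration will be effectuated by qualified nurses", at home where a home care service is organised. On what that service writes down: "In addition, the home care service will record the administration on a separate log". The Control intervention section describes no matching contact unless a control patient comes to need parenteral nutrition.
- **Scheduled AE assessment.** Data collection and management states, without splitting by arm: "During NACT, three study visits will be performed where ECOG score, as well as AEs and SAEs will be assessed and documented". Its account of visit 4 names all patients.
- **Reporting window.** The section on safety evaluation and AE reporting sets a continuous window: "All AEs/SAEs from the moment of randomization until the last study visit have to be assessed, documented, and reported". The local investigator or a sub-investigator does this. Postoperative and surgical complications are not recorded as AEs. Expected laboratory changes below grade 3 during chemotherapy are also exempt, in both arms.
- **Blinding.** Randomization and blinding says that patients cannot be blinded. The blinded observers see only the surgical file, not the oncological one.
- **Analysis.** Secondary endpoint 1 under Outcome measures is the "rate of serious adverse events (SAEs) and adverse events (AEs) during NACT". The Safety analysis section adds: "All AE/SAEs will be analyzed with incidence rates by treatment group and according to their severity". It names Chi-square and Fisher's exact tests for group comparisons, where appropriate, on patients as treated.

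**The concern.** The reporting window is continuous, so an event that comes to the investigator's notice between visits counts. A patient seen by a nurse every day has more chances for a brief episode of nausea, diarrhoea, mild fever or port-site redness to be noticed and passed on. A control patient may have forgotten it by the next visit. Observer blinding gives no protection, because AE reporting belongs to the local investigator. Postoperative complications lie outside AE reporting, so the comparison rests mainly on the preoperative period, which is when contact differs.

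At stake is the reading of low-grade toxicity. Equal true rates could look like harm from parenteral nutrition, or a real reduction in chemotherapy toxicity could be hidden. A larger sample would not remove such an error. The article acknowledges a slightly raised risk of port infection, and AE reports feed the regular risk-benefit reassessment, so an AE difference that cannot be interpreted has a cost.

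**Working it through.** The article gives no AE incidence and no detection probability, so there is no figure of the plan to reproduce on this point. The check has two parts.

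**1. What differs between arms and what does not**

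| Feature | Parenteral nutrition | Control |
|---|---|---|
| Scheduled AE visits in NACT | three | three |
| AE window and assessor | continuous, local investigator | the same |
| Routine toxicity evaluation | yes | yes |
| Daily nurse contact to surgery | yes | none described |
| Stated nurse duty to report AEs | none | not applicable |

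The difference lies in opportunity for unscheduled detection, not in the schedule. As a rough guide to its extent, 32 months in total less 27 months of recruitment leaves 5 months per patient. That gives 5 × 30.4 − 30 = 122 days before surgery at most, which allows up to about 100 nurse contacts. These are planning timelines, not a stated treatment duration.

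**2. What unequal detection would do to the test**

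Inputs: n = 75 per arm (Sample size section). Assumed: the same true per-patient incidence p in both arms, full detection with parenteral nutrition, and a relative loss s in controls. The observed incidences are then p and p(1 − s). The rejection probability is the sum, over all pairs of counts, of the two binomial probabilities multiplied together wherever |z| > 1.96. Here z = (difference in proportions) / √[2·p̄(1 − p̄)/75], and p̄ is the pooled proportion.

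One cell by hand: p = 0.5 and s = 0.2 give 0.50 against 0.40, so p̄ = 0.45. The standard error is √(2 × 0.45 × 0.55/75) = 0.081, and the expected z is 0.10/0.081 = 1.23. Exact enumeration gives a rejection probability of 25.0%.

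| True incidence | s = 10% | s = 20% | s = 30% |
|---|---|---|---|
| 30% | 6.8% | 12.9% | 24.2% |
| 50% | 10.2% | 25.0% | 48.2% |
| 70% | 14.6% | 43.5% | 76.5% |

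With s = 0 and p = 0.5 the rate is 5.5%, so the excess comes from detection alone. For s of 20% or more, nearly all rejections point against parenteral nutrition.

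Milder assumptions: 95% detection with parenteral nutrition and 90% in controls give an observed risk ratio of 0.95/0.90 = 1.06. The false-positive rates are then 5.4%, 5.9% and 7.3% at true incidences of 20%, 40% and 60%. Control detection of 70% gives a ratio of 1.36 and rates of 13.2%, 25.2% and 46.8%. Fisher's exact test gives lower rates in the same pattern.

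Masking, also on assumed values: with true incidences of 45% (parenteral nutrition) and 60% (control), power is 47% under full detection. If controls lose 20%, their observed incidence is 0.60 × 0.80 = 48%, and power falls to 7%.

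**The case against.** A reader might infer that controls alone are asked about AEs at study visits, or that the comparison is biased and always against parenteral nutrition. The documents do not support either reading.

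- Visit-based assessment applies to both arms, with the same window and the same assessor.
- No section makes nurses elicit or forward AEs; their log covers administration. The route from nurse to AE record is an inference.
- The weekly calorie recalculation takes place within routine clinical evaluation during NACT, and the Risks section refers to routine checks of chemotherapy toxicity. Controls are therefore also seen outside study visits.
- The direction is plausible, not certain. Controls with poor intake may receive parenteral nutrition. The as-treated safety analysis then counts them in that group, possibly with more events for reasons unrelated to detection. In the intention-to-treat analysis of endpoint 1 they would dilute a contrast.
- Secondary endpoints are analysed descriptively and any testing is explorative, so no confirmatory conclusion depends on this.
- The incidence is per patient. Someone with recurrent nausea counts once any episode is reported, so missed episodes do not become missed patients one for one.
- The plan already reports by severity and lists related events separately.

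All of this stands, and it limits both certainty and size. None of it is a safeguard against unequal contact, and the article describes none. Nor is the point just a detail left to an analysis plan: the article itself fixes the crude comparison, and the source of a report cannot reliably be recovered if it was not recorded at the time.

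A further objection concerns the remedy. Taking low-grade events known only through home care out of the comparison could hide real harm, such as an early port infection. That is correct, so the all-AE comparison should stay.

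**Conclusion.** The point holds as a risk of differential ascertainment of grade 1-2 events in the crude all-AE comparison and in the AE rate during NACT, most plausibly against parenteral nutrition. SAEs and grade 3 or higher events should be little affected; SAEs must be reported within 24 hours in both arms.

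The size is unknown. The range of about 7% to 77% rests wholly on an assumed 10% to 30% relative loss of detection in controls and assumed true incidences of 30% to 70%. Its upper end needs full detection with parenteral nutrition, a 30% loss in controls and a 70% incidence, and should not be read as an estimate. If routine toxicity checks capture most events in both arms, the rate stays near 5%. The primary endpoint is not touched by this point. The change is worth making because it is cheap while recruitment is still only planned.

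**What to change.** In Outcome measures and Safety analysis:

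1. Keep the all-AE incidence table and its comparison.
2. Add a pre-specified comparison on equally ascertained events: all SAEs and all CTCAE grade 3 or higher events from any source, plus grade 1-2 events elicited at the common NACT visits with the same question list in both arms.
3. Base any between-arm statement about low-grade toxicity on that second comparison.
4. Add one eCRF field for the source of each AE report (study visit, home care service, other).
5. Show events known only through home care contact separately, including any port-site events, without dropping them from the safety tables.

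The cost is one eCRF field, a fixed question list at existing visits and one more table; no visit is added. The low-grade comparison will rest on fewer events. Nurse contact could still prompt recall at the common visits, so the change reduces unequal ascertainment but does not guarantee its removal. The source field will show how many events came to light only through home care.

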### Withdrawals

Patients are free to withdraw from trial participation at their own request at any time and without giving reasons for their decisions. Withdrawals will be documented in the eCRF and in the patient’s medical record. However, all ongoing SAEs must be followed up and documented until their final outcome can be determined. Patients that withdraw their consent or are excluded from the trial due to the decision of the sponsor or investigator will be replaced to ensure a sufficient sample size. Drop-outs (e.g. lost to follow up) have been taken into account at sample size calculation and will not be replaced.

### Stopping guidelines

The trial can be prematurely closed by the sponsor in consultation with the responsible biostatistician for the following reasons: (1) it appears that patients’ enrolment is unsatisfactory with respect to quality or quantity, or data recording is severely inaccurate or incomplete; and (2) there is external evidence demanding a termination of the trial, e.g. indicating that the rate or severity of SAEs or morbidity in this trial poses a potential health hazard caused by the intervention in one of the trial groups. In case of premature closure, the ethics committee and health authorities must be informed.

### Registration

The trial protocol was registered at the German Clinical Trials Register (part of the WHO International Clinical Trials Registry Platform) under number DRKS00009451 on 3 July 2017.

### Good clinical practice

The procedures set out in this trial protocol, pertaining to the conduct, evaluation, and documentation of this trial, are designed to ensure that all persons involved in the trial abide by GCP [16] and the ethical principles described in the current version of the Declaration of Helsinki [4]. The trial will be carried out in compliance with German Drug Law (AMG) [15] as well as all other local legal and regulatory requirements.

## Discussion

The PERCOG trial has a pragmatic, two-armed study design (parenteral nutrition vs no parenteral nutrition during NACT) and shall be conducted in four centers within the German Surgical Trial network CHIR-*Net*. A multicenter approach was chosen to increase external validity. Internal validity and data quality assurance are established by adherence to the SPIRIT guideline and GCP regulations, regarding recruitment, training of study personnel, methods against bias, outcome reporting, and documentation.

All patients suffering from non-metastatic gastric or esophago-gastric cancer, staged at least uT2N+ receiving NACT, will be screened within 27 months. Specialized oncological surgical centers were chosen and broad inclusion criteria were applied to ensure rapid and sufficient recruitment to achieve the target sample size.

The primary endpoint is the postoperative CCI, which was recently demonstrated to be a superior and sensitive outcome measure for RCTs in surgery [5]. Since reporting of postoperative complications is often non-standardized and incomplete, surgical trials can be difficult to compare. The CCI includes all types of postoperative complications independent of their severity and has been shown to be more sensitive than other existing morbidity endpoints [3–5].

The results of this pragmatic trial will provide high-level evidence for clinical recommendations regarding the effectiveness of preoperative parenteral nutrition during NACT of patients with gastric or esophago-gastric cancer.

### Trial status

Recruitment is planned to start in January 2018.

## Abbreviations

AE: Adverse event
AMG: *Arzneimittelgesetz*/German Drug Law
ASA: American Society of Anesthesiologists
BMI: Body mass index
CCI: Comprehensive Complication Index
COPD: Chronic obstructive pulmonary disease
CTCAE: Common Terminology Criteria for Adverse Events
ECOG: Eastern Cooperative Oncology Group
eCRF: Electronic case report form
EORTC: European Organization for Research and Treatment of Cancer
GCP: Good Clinical Practice
GIT: Gastrointestinal tract
ICH: International Conference on Harmonization of Technical Requirements for Registration of Pharmaceuticals for Human Use
ICU: Intensive care unit
ITT: Intention-to-treat
KKS: *Koordinierungszentren für Klinische Studien*/German Network of Coordinating Centers for Clinical Trials
MSZ: *Münchner Studienzentrum*/Munich Centre of Clinical Studies
NRS: Nutritional Risk Score
NYHA: New York Heart Association
PP: Per protocol
QoL: Quality of life
RCT: Randomized controlled trial
SAE: Serious adverse event
SUSAR: Suspected unexpected serious adverse reaction
TUM: *Technische Universität München*/Technical University of Munich
